### Randomization

The patients will be randomized to one of the study groups using a computer-generated list. Allocation concealment will be ensured by enclosing assignments in sealed, opaque, sequentially numbered envelopes, which will only be opened when the general narcosis of the study patient has been established [26].

Postoperative outcomes and sequalae will be assessed by an outcome assessor who is a gynecologist in a subspecialization program in urogynecology and also well trained in the transvaginal mesh operation. The outcome assessor will remain blinded to the type of intervention throughout the study.

#### Blinding

Participants will be blinded against the type of TVM surgery received (original TVM vs mTVM). The participant information document will not provide any information on the differences in surgical protocols such that the women could ascertain their group allocation. All investigators involved in data acquisition, data analyses, and statistics will also be blinded against group allocation. The surgeons in charge of the therapy cannot be blinded against group allocation and therefore will not be involved in data acquisition, data reduction, data analyses, or statistics.

### Measurement outcomes

Baseline (before intervention phase) and follow-up measurements (of primary, secondary, and tertiary outcomes) after six weeks to three years will be performed at the Division of Urogynaecology, Department of Obstetrics and Gynaecology, University of Szeged, Hungary, by an experienced urogynecologist who will be blinded to group allocation of participants and who will not operate on the patients (Table 1).

### Primary endpoints

The primary outcome measures will be a significant improvement in POP repair and objective cure of SUI after the surgery. The efficacy of POP repair will be understood as a significant (> 3 cm) improvement during follow-up at points Aa, Ba, C, and D using the POP–Q system (International Continence Society) [19, 20]. Anti-incontinence efficacy is classified as no further SUI, as diagnosed by cough tests and urodynamic examinations. Besides the gynecological and urodynamic examinations, sonographic findings from introital ultrasound examinations will be analyzed in terms of anatomical success both before and following surgery and during follow-up.

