**Methods:**

One hundred and thirty patients diagnosed with POP–Q II–III and concomitant SUI requiring surgical treatment will be included in this prospective, randomized, double-blind, controlled clinical trial. Patients will be randomly allocated to receive either original TVM (TVM group, *n* = 65) or modified TVM surgery (mTVM group, *n* = 65). As the primary outcome parameter, we will evaluate the objective SUI and POP cure rates. Secondary endpoints include postoperative morbidity as assessed with the International Urogynaecological Association classification and subjective prolapse and incontinence cure rates reported by questionnaires.

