#### Participants considered for trial

This will be a prospective longitudinal study involving all patients successively scheduled for operation for symptomatic prolapse POP–Q grade II or III and coexisting SUI, who will be included in the study after informed consent has been obtained. Patients will be recruited in the Department of Obstetrics and Gynaecology at the University of Szeged. The study will be conducted for an estimated maximum of 18 months (between August 2016 and December 2017). Table 1 provides an overview of the patient recruitment and evaluation plan.

**Table 1 Tab1:** Schedule of assessments/data collection

Assessment	Recruitment before intervention phase	Intervention (surgery)	Follow-up				
			6 weeks	6 months	1 years	2 years	3 years
Assessment of eligibility criteria	x						
Written informed consent	x						
Gynecological examination: incontinence symptoms	x	x	x	x	x	x	x
Gynecological examination: prolapse	x	x	x	x	x	x	x
Urodynamic examination	x				x		x
Adverse events		x	x	x	x	x	x
Questionnaires: PISQ-12 and PFDI	x		x	x	x	x	x
Introital sonography	x				x		x
Urine culture	x			x	x	x	x

The symptomatic POP–Q Stage II–III (determined by the gynecological examination using the International Continence Society quantification system) [18] anterior vaginal wall prolapse is defined as the maximum extent of the prolapsed anterior and middle compartments being within 1 cm above and 6 cm below the hymen [19, 20]. According to the international POP guidelines (the EBU and NICE guidelines) [21, 22], if the condition disrupts the patient’s life and non-surgical treatment options have not helped, it should be treated surgically.

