## Statistical methods

### Hypothesis

Alternative hypothesis for primary outcome: it is hypothesized that the group undergoing the modified transvaginal mesh operation will have a statistically higher improvement of continence measured by gynecological and urodynamic examination, and from the questionnaire administered before and after the intervention phase.

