#### Sample size calculation

As we have newly developed the modification to the prosthesis surgery, an exploratory pilot study was designed to evaluate the feasibility of the modification to the mesh for the treatment of SUI. Twenty patients with SUI and POP were recruited for a mTVM operation by the same two senior surgeons who are conducting this randomization study. The sample size calculation study was designed based on preliminary data on the 20 patients. The newly developed technique yielded an objective SUI cure rate of 92% as opposed to 72% for the original TVM published by Sergent et al. [13, 17]. Sample size calculations were performed with G*Power software [29], using the statistical model for an χ^2^ approach. Consequently, sample size was estimated theoretically and an effect size of = 0.1, indicating a small effect, will be accepted. The sample size was calculated for the primary outcome of the SUI cure rate with the following assumptions: α = 0.05, power (1–β error probability) = 0.8, number of groups = 2. Based on these assumptions, a total sample size of *N* = 130 was estimated. In anticipation of dropouts (10%: *n* = 16) or a violation of protocol (10%: *n* = 16), a final sample size of *N* = 162 (81 participants per group) results.

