### Statistical analyses

Analysis of the patients will follow the CONSORT flow diagram (Fig. 1) through the phases of the study (enrollment [assessed, excluded, randomized], allocation [control group and experimental group with intervention received or not received], follow-up [lost to follow-up, discontinued intervention] and analysis) [30].

All statistical analyses will be conducted using SPSS software version 22 (IBM, Armonk, NY, USA). All tests will be two-sided and significance will be set at *P* < 0.05. Efficacy measurements were adjusted by intention-to-treat analysis. Missing values will be replaced using the last observation carried forward (LOCF) method. No subgroup analyses are planned. Standard deviations, 95% confidence intervals, and median will be used for the descriptive analyses. Primary and secondary outcome analysis: the Chi-square test or Fisher’s exact test will be employed to identify any objective outcome differences among groups.

Generally, continuous data will be checked for normality using the Shapiro–Wilk test. If the normality assumption is violated, then PISQ-12 and PFDI scores as tertiary outcomes will be normalized by log transformation (log10(x)). Univariate-repeated measure analysis of variance (ANOVA) will be used to determine the secondary outcome between and within the two groups (mTVM, TVM group) at six endpoints (before intervention and during follow-up clinical appointments 1–5 following intervention). Mixed design ANOVA will be carried out to determine the effects of the modified operation on subjective cure rate for POP and SUI, and the Bonferroni post hoc test will be used to test the difference between means. All statistical analyses will be completed after the final measurement of the last patient during the last clinical appointment after intervention. The repeated measure design with seven points in time allows us to monitor how patients change over time in both short-term (before/during intervention) and long-term situations (before/after intervention).

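### The primary endpoint is stated inconsistently, no primary visit is named, and SUI cure as defined can be observed at only two of the five follow-up visits

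*Protocol article*

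**What the plan says.** The protocol article describes the primary endpoint in four places.

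- **Abstract, Methods:** "As the primary outcome parameter, we will evaluate the objective SUI and POP cure rates". Questionnaire-based subjective cure is listed there as secondary.
- **Primary endpoints:** "The primary outcome measures will be a significant improvement in POP repair and objective cure of SUI after the surgery". SUI cure is defined thus: "Anti-incontinence efficacy is classified as no further SUI, as diagnosed by cough tests and urodynamic examinations". POP success is a change of more than 3 cm, described as "improvement during follow-up at points Aa, Ba, C, and D using the POP–Q system".
- **Hypothesis:** the alternative hypothesis for the primary outcome concerns continence. It is measured by gynecological and urodynamic examination "and from the questionnaire administered before and after the intervention phase". POP does not appear.
- **Sample size calculation:** "The sample size was calculated for the primary outcome of the SUI cure rate", with 92% against 72%, α = 0.05 and power 0.8.

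On timing, the Measurement outcomes section has primary, secondary and tertiary outcomes all measured from six weeks to three years. Table 1 lists five postoperative visits: 6 weeks, 6 months, 1, 2 and 3 years. Its row "Urodynamic examination" is marked at recruitment, 1 year and 3 years only.

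On testing, the Statistical analyses section says "All tests will be two-sided and significance will be set at" P < 0.05. Objective outcomes get a chi-square or Fisher test, with no visit named. The one adjustment mentioned, a Bonferroni post hoc test, belongs to comparisons of means in the mixed-design ANOVA of subjective cure. The same section calls the PISQ-12 and PFDI scores tertiary. All analyses are completed after the last patient's final appointment.

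**The concern.** A reader of the final report must be able to say which single result decides the trial. Here the text leaves three choices open: which outcome or combination of outcomes counts, at which visit, and whether the questionnaire belongs to the primary claim. Because the analysis follows the last visit, nothing in the document settles these choices before the data from every visit exist.

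There is also a conflict that does not depend on multiplicity. The SUI definition needs an examination that the schedule omits at three of the five visits.

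At stake are the false-positive rate of the primary claim, if either outcome or any visit may carry it, and its power, if both outcomes must succeed.

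**Working it through.** **1. The plan's own figure.** The target before dropout is N = 130, or 65 per group, for SUI cure of 72% against 92%, two-sided α = 0.05, power 0.80. The pooled normal formula is

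n = [1.96·√(2·0.82·0.18) + 0.8416·√(0.72·0.28 + 0.92·0.08)]² / 0.20² = (1.065 + 0.442)² / 0.04 ≈ 56.7, so 57 per group (N = 114).

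With continuity correction it is 67 per group (N = 134). Exact Fisher power first reaches 80% at 64 per group (N = 128, power 0.806) and is 0.814 at 65. So 130 fits one Fisher test of one outcome, with the whole 0.05 spent on SUI cure. Nothing is set aside for POP, for a second visit or for the questionnaire. (The stated effect size of 0.1 does not lead to 130; that is a separate matter.)

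**2. The sections side by side.**

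| Section | POP | Objective SUI cure | Questionnaire |
|---|---|---|---|
| Abstract | primary | primary | secondary |
| Primary endpoints; Secondary and tertiary endpoints | primary | primary | tertiary |
| Hypothesis | absent | primary | in the primary hypothesis |
| Sample size calculation | absent | primary | absent |
| Statistical analyses | objective outcome, rank not given | objective outcome, rank not given | tertiary |

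**3. Definition against schedule.**

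| Visit | Urodynamics in Table 1 | SUI cure observable as defined |
|---|---|---|
| 6 weeks | no | no |
| 6 months | no | no |
| 1 year | yes | yes |
| 2 years | no | no |
| 3 years | yes | yes |

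The planned last-observation-carried-forward rule could bring a 1-year urodynamic result to 2 years. At 6 weeks and 6 months there is no postoperative urodynamic result to carry.

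**4. Type I error if success on either outcome were allowed.** The number of tests that can be made as defined is 2 (SUI at 1 and 3 years) + 5 (POP at every visit, counted as one test per visit) = 7. For k independent tests at 0.05 the chance of at least one false positive is 1 − 0.95^k:

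- k = 2 (two outcomes, one visit): 1 − 0.95² = 9.75%
- k = 4 (two outcomes, 1 and 3 years): 1 − 0.95⁴ = 18.5%
- k = 7: 1 − 0.95⁷ = 30.2%

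Repeated visits are correlated, so the last two overstate. The documents give no correlations; these are assumptions.

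- *Simulated binary data:* 65 per group; 82% success in both groups, the mean of 72% and 92%; latent visit correlation 0.5–0.9; latent cross-outcome correlation 0.2; chi-square at 0.05. Results: 9–10% for two outcomes at one visit, 15–18% at 1 and 3 years, 21–27% for the seven tests.
- *Correlated z-statistics:* visit correlation 0.5–0.9, with cross-outcome correlation set at 0.3 times that. Result for the seven tests: 25% falling to 16%.

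The two ranges differ largely because a latent correlation of 0.9 is only about 0.68 between the binary outcomes. Together they give 16–27%.

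**5. If both outcomes must succeed.** In the same simulation both were falsely significant at one visit in about 0.2% of trials, so there is no inflation. The cost falls on power. With SUI power 0.814 and, purely for illustration, POP power 0.80 and independence, joint power is 0.814 × 0.80 = 0.65. The documents state no POP effect, so the true figure cannot be derived.

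**6. If alpha were split equally** (0.025 each), power for SUI at 65 per group falls from 0.852 to 0.774 by the pooled formula, or from 0.814 to 0.727 by Fisher. N rises from 114 to 138, or from 134 to 158 with continuity correction.

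**The case against.** The best defense is that the lead outcome is recognizable. The abstract frames the trial as a test of anti-incontinence superiority, the Hypothesis section is about continence, and only SUI cure is powered. On that view POP is a surplus primary label. A detailed multiplicity procedure may also sit in an analysis plan that is not shown. Both arguments have weight, and the absence of a multiplicity procedure would not be a finding by itself. They do not remove the contradictions between sections, the missing primary visit, or the mismatch between the SUI definition and Table 1, which belong to the protocol.

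Three stronger readings are tempting but not supported:

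- A reader might infer that a win on either outcome at any visit makes the trial positive. No section says so. The Primary endpoints section joins the outcomes with a plain conjunction and gives no success rule.
- A reader might infer that the primary outcomes are tested at all five visits and count ten tests, which gives roughly 19–37% under the two sets of correlation assumptions. The Statistical analyses section leaves the visit open for these tests, and the count includes SUI at three visits where it cannot be observed as defined.
- A reader might infer that a laxer SUI endpoint will be used where urodynamics are missing. Nothing states this. The text supports only that definition and schedule do not match.

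**Conclusion.** The point holds as an inconsistency that must be corrected. The outcome or outcomes that decide the trial, the success rule and the visit are not fixed, and the questionnaire has three different ranks. SUI cure as defined is observable at 2 of 5 follow-up visits. These findings come from the text and rest on no assumption.

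The size of the error is conditional. It exceeds 5% only if either outcome, or more than one visit, may carry the claim. The range from about 9–10% to 16–27% then depends on the assumed correlations and on the number of visits used. If both outcomes are required, the type I error is safe and the unknown is joint power. The error rates describe what the wording permits, not what the protocol says will be done.

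**What to change.** Name one primary endpoint: objective SUI cure, meaning a negative cough test and no urodynamic SUI, at the 12-month visit. It is the powered outcome and urodynamics are scheduled then. The section on concealment of allocation also has participants told their treatment only after completing the 12-month forms. Test POP success at 12 months as key secondary at 0.05, only if SUI is significant (fixed sequence). Treat all other visits as secondary, and remove the questionnaire from the primary hypothesis. Align the Abstract, Primary endpoints, Hypothesis and Statistical analyses sections with this.

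The cost is wording only. Alpha stays at 0.05 and the SUI sample size of 130 is not affected by this change. The downside is that POP and the 3-year results lose primary status.

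Other choices would also resolve the ambiguity: SUI cure at 3 years as primary, where urodynamics are scheduled and the assessor is to remain blinded, or requiring both outcomes at one named visit with joint power stated.

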Therefore, the research group developed a modification to the transobturator four-arm TVM [13, 17] to increase its anti-incontinence effect. While the sling is located beneath the mid-urethra, the TVM elevates the distal part of the anterior vaginal wall [13, 17]. In the original TVM, the posterior part of the mesh is anchored to the anterior aspect of the cervix and the anterior arms are spread under the bladder neck with stabilizing sutures. We hypothesize that the original TVM operation can be followed by residual SUI since the strengthening of the back arms may result in a backward dislocation of the entire mesh. The posterior movement of the mesh allows the dorsal rotation of the urethra since the mid-urethra is not suspended. The proposed modification to the original surgical procedure includes the suture of the anterior part of the mesh to the mid-urethra to prevent the mesh sliding. We think that the appropriate elevation of the mid-urethra would thus occur with the anterior arms and that would achieve a more effective anti-incontinence. The pubourethral ligament is usually loose in SUI, but the anchored mesh would theoretically normalize its function and stabilize the urethra. Intra- and postoperative complication rates would be expected to be similar to those with the original four-arm TVM, but the modified TVM with the anchoring suture would be slightly superior with respect to POP repair and remarkably more effective in SUI correction. In our preliminary study, the anterior fixing of the TVM to the mid*-*urethra demonstrates as high an efficacy of anti-incontinence as 96.8% and an enormously reduced recurrence prolapse rate of 3.2% in (unpublished data). The mesh extrusion rate is particularly low and this may be due to the fact that the stabilizing sutures exert a lack of “folding/wrinkling” of the edge of the mesh, preventing a lifting up of the mesh which does not compress the mucosa and derange the periprosthetic vasculature.

A further modification to the TVM surgery is that the positioning of the mesh will occur 1.5 cm below the urethral meatus, leading to an elevation of the entire anterior vaginal wall including the anterior and middle compartments as well. By contrast, the original TVM surgery does not prevent anterior compartment prolapse [13, 17].

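### POP repair, a primary outcome measured in centimetres, is tested only as a yes/no >3 cm change without baseline adjustment; the power loss is real, but its size can only be given as a range

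*Protocol article*

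**What the plan says.** The abstract treats both objective outcomes as rates: "As the primary outcome parameter, we will evaluate the objective SUI and POP cure rates". The Primary endpoints section defines the prolapse part: "The efficacy of POP repair will be understood as a significant (> 3 cm) improvement during follow-up at points Aa, Ba, C, and D".

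The Statistical analyses section gives the test: "Primary and secondary outcome analysis: the Chi-square test or Fisher’s exact test will be employed to identify any objective outcome differences among groups". It names two further methods. A repeated-measures ANOVA "will be used to determine the secondary outcome between and within the two groups", and a mixed-design ANOVA is assigned to subjective cure. Neither is assigned to the primary POP outcome.

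Three other places matter:
- Table 1 schedules a prolapse examination at recruitment, at surgery, and at 6 weeks, 6 months, 1 year, 2 years and 3 years.
- Under Participants considered for trial, eligible prolapse is defined by "the maximum extent of the prolapsed anterior and middle compartments being within 1 cm above and 6 cm below the hymen".
- The Background expects that "the modified TVM with the anchoring suture would be slightly superior with respect to POP repair and remarkably more effective in SUI correction".

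The Hypothesis and Sample size calculation sections concern continence and SUI cure only. No effect size, SD, success rate or power is given for POP.

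**The concern.** POP-Q positions are recorded in centimetres. Cutting the change at 3 cm treats an improvement of 3.1 cm like one of 6 cm, and 2.9 cm like none. When the expected benefit is small, that lost information is hard to spare.

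The cut is also applied to raw change, while starting positions differ widely. How likely a woman is to pass 3 cm then depends partly on where she started. That variation has nothing to do with the operation, and an unadjusted two-by-two test leaves it in as noise.

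At stake is a primary comparison that could report no POP difference from data that would show one if analysed on their own scale.

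**Working it through.** **The plan's own figure.** The only stated size is N = 130 (65 per arm) for SUI cure of 72% against 92%, two-sided 0.05, power 0.80. Exact enumeration for Fisher's test gives 128, with power 81.4% at 130, so the figure is close to what those rates require. (The effect size of 0.1 quoted beside it would need 785, which is a separate matter.) There is no POP power figure to reproduce.

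**Inputs for POP.** From the document: 1:1 allocation, two-sided 0.05, 65 per arm (81 per arm with the allowance for dropouts and violations). Assumed, because not given: normally distributed change with equal SD in both arms, a true difference of d SDs, and a share p0 of controls passing 3 cm.

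**Step 1: the cut alone.**
- Full scale: power = Φ(d√(n/2) − 1.96). For d = 0.5, n = 65: Φ(0.5 × 5.70 − 1.96) = Φ(0.89) = 81.3%.
- Cut: p1 = Φ(Φ⁻¹(p0) + d) and p̄ = (p0 + p1)/2. Power = Φ{[(p1 − p0)√n − 1.96√(2p̄(1 − p̄))] / √(p0(1 − p0) + p1(1 − p1))}.
- Example, p0 = 80%, d = 0.5: p1 = Φ(0.842 + 0.5) = 91.0% and p̄ = 0.855. The numerator is 0.888 − 0.976 = −0.088, the denominator is 0.492, and the power is Φ(−0.18) = 42.9%.

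Power at 65 per arm:

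| d | Full scale | Cut, p0 = 50% | 70% | 80% | 90% |
|---|---|---|---|---|---|
| 0.5 | 81.3% | 60.6% | 51.8% | 42.9% | 29.0% |
| 0.3 | 40.1% | 27.1% | 23.7% | 20.2% | 14.7% |
| 0.2 | 20.6% | 14.5% | 13.2% | 11.6% | 9.1% |

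Share of power lost (1 − cut/full scale), for p0 = 50%, 70%, 80% and 90%:
- d = 0.5: 25%, 36%, 47%, 64%
- d = 0.3: 33%, 41%, 50%, 63%
- d = 0.2: 30%, 36%, 44%, 56%

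Fisher's test, also permitted, is lower still: 54.8%, 44.3%, 34.3% and 16.6% at d = 0.5. At 81 per arm and d = 0.5 the comparison is 89% against 70% to 35%. The share of information kept by the cut, φ(c)²/[p0(1 − p0)] with c = Φ⁻¹(p0), is 64%, 58%, 49% and 34%.

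**Step 2: baseline left unadjusted.** The eligible range runs from 1 cm above to 6 cm below the hymen, which is 7 cm.
- A woman starting 6 cm below who gains 3.1 cm counts as a success at 2.9 cm below, still inside the eligibility range.
- A woman starting 1 cm above must finish more than 1 + 3 = 4 cm above.

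An illustrative simulation used 4,000 runs per setting, 65 per arm, one position per woman, mean postoperative position 2 cm above the hymen with SD 1.0 cm, a true gain of 0.5 cm, and slope on baseline from 0 to 0.6. Only the baseline range comes from the document.
- Baseline uniform over the full 7 cm: Chi-square power about 15% to 25%, ANCOVA about 80%.
- Baseline uniform from 1 cm above to 3 cm below: Chi-square from about 25% to just over 50% (upper end 51% to 54% between runs), ANCOVA about 80%.
- SD 1.5 cm instead: Chi-square about 13% to 31%, ANCOVA about 44% to 49%.

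ANCOVA was ahead in every setting tried, but the size of the gain depends on the assumptions.

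**The case against.** The strongest reply is that a responder outcome is a legitimate choice. The protocol asks for cure rates, names a threshold and pairs it with a matching test. A proportion passing 3 cm and a mean difference in cm answer different questions, so this is neither an arithmetic error nor a contradiction. That stands, and it is why the >3 cm proportion should stay in the report. It does not explain why the centimetre data and the baseline go unused for a primary outcome on which only a slight advantage is expected.

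Second, POP lies outside the stated hypothesis and the sample size basis. True, but it is still listed as primary.

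Third, the simulation's SD, postoperative mean, slope and uniform baseline are assumptions. It follows one position per woman, whereas the protocol names four points. The 7 cm range describes the maximum extent of prolapse, not each of Aa, Ba, C and D. All of this stands, so the simulation shows direction and plausibility rather than a prediction.

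A reader might also infer three stronger things that the document does not support:
- **That the cut throws away most of the power.** For the cut alone this needs about 80% to 90% or more of controls to pass 3 cm, and no such rate is given. The 3.2% prolapse recurrence in the Background is for the modified operation and is not the >3 cm rule.
- **That the 3 cm threshold has no published basis.** The sentence cites two references that cannot be examined here.
- **That the size of the loss is the same however the four points are combined.** The success rate, and with it the loss, depends on whether all or any points must pass and at which visit. The text fixes neither.

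**Conclusion.** The point holds as an inefficient stated analysis of a primary outcome. Under normal change scores and 50% to 90% control success, the cut alone costs about a quarter to two-thirds of the power at 65 per arm. Leaving out baseline can increase that: in the SD 1.0 cm, 0.5 cm gain illustration, Chi-square has about 15% to just over 50% power against about 80% for ANCOVA.

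The limit matters as much. With d = 0.2 the unadjusted full-scale test has about 21% power and would need 393 per arm for 80%. Changing the analysis makes better use of the data but does not make the trial adequately powered for a slight POP benefit, since it was sized for SUI only. The change is worth making because it is cheap, not because it secures the POP conclusion.

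**What to change.** In the Primary endpoints and Statistical analyses sections:
1. Name one leading POP-Q point and one visit for the POP comparison (Ba is a possible example; the choice is the sponsor's). Treat the other points as supportive.
2. Compare the arms on position in cm by ANCOVA, with postoperative position modelled on arm and baseline position. A mixed model over the five follow-up visits with baseline as covariate is an alternative.
3. Report the adjusted mean difference in cm with its 95% CI. If postoperative positions are skewed, add a rank-based or bootstrap check.
4. Keep the >3 cm proportion by arm as a reported responder outcome, stating how the four points combine and at which visit.
5. Leave the SUI comparison unchanged.

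No new visits, measurements or patients are needed, and the named software fits these models. There are two costs. The POP comparison becomes a mean difference rather than a cure rate, which the retained proportion largely offsets. And because recruitment began on 22 August 2016, changing how a primary outcome is analysed must be documented as an amendment before any unblinded analysis.

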#### Exclusion criteria

Exclusion criteria are: urge, mixed incontinence or occult SUI; prolapse < grade II or > grade III POP–Q ([21, 22], https://uroweb.org/guideline/urinary-incontinence), apical or posterior compartment prolapse, dysuria (bladder tumor, neurogenic urinary bladder damage), a history of mesh use or anti-incontinence pelvic procedures; pregnancy (urine test to accomplish); lactation period not yet finished; current urinary tract or vaginal infection, menstruation on the day of examination; contraindications for measurements or interventions, for example, acute inflammatory or infectious disease, tumor or fracture; de novo systemic or local estrogen treatment (< 3 months); de novo drug treatment with anticholinergics or other bladder active substances (tricyclic antidepressants and selective serotonin reuptake inhibitors) and cancer of the pelvic organs.

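### The primary POP success rule scores change (more than 3 cm), not final position: it can credit prolapse that remains and, given the POP-Q scale limit, cannot be met at Aa or Ba by women starting at or above the hymen

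*Protocol article*

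**What the plan says.** Under Primary endpoints: "The primary outcome measures will be a significant improvement in POP repair and objective cure of SUI after the surgery". Efficacy of POP repair is then fixed as more than 3 cm of "improvement during follow-up at points Aa, Ba, C, and D". No final stage or position is required, and the text does not say how the four points combine. The abstract describes the same outcome as a rate of cure: "we will evaluate the objective SUI and POP cure rates". Statistical analyses assigns the Chi-square or Fisher's exact test to primary outcomes, so each woman has to be classed as a success or a failure.

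On who enters, Participants considered for trial defines eligible stage II–III prolapse as the "maximum extent of the prolapsed anterior and middle compartments being within 1 cm above and 6 cm below the hymen". Exclusion criteria rules out "prolapse < grade II or > grade III" and also "apical or posterior compartment prolapse". The Background says that the modified operation lifts the anterior and middle compartments, and the Discussion describes TVM as the standard operation for middle-compartment stage II–III prolapse.

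**The concern.** A fixed change threshold takes no account of where the woman started. Applied to an entry range 7 cm wide, it can misclassify at both ends. A large prolapse can improve by the required amount and still be a prolapse by the trial's own definition. A small one may have no room to improve that much, even if it is fully corrected.

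The result would be reported as a cure rate but would depend heavily on baseline severity. That costs interpretability and blunts the comparison between arms. It matters more here because the Background expects only a slight advantage of the modified operation on POP repair.

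The rule also scores C and D, the apical points of POP-Q, while the eligibility text points two ways on whether apical or middle-compartment descent is in the trial.

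**Working it through.** The plan gives no POP success rate to reproduce; the check is arithmetic on positions. Positions are in cm relative to the hymen, negative above and positive below.

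**Inputs**
- Success threshold: gain greater than 3 cm (Primary endpoints).
- Eligible extent: -1 to +6 (Participants considered for trial).
- Best attainable position L of Aa and Ba: not in the article. Taken as -3, the scale limit of the POP-Q system that the article names. This is an assumption, varied below from -3 to -5.

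**1. Success with prolapse remaining (documents' figures only).** Final position = start - gain. With a gain just over 3, the point is still at -1 or lower down whenever start - 3 > -1, that is, start > +2. With a gain of 3.5 cm:

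| Start | Final | Inside -1 to +6? |
|---|---|---|
| +2 | -1.5 | no |
| +3 | -0.5 | yes |
| +4 | +0.5 | yes |
| +5 | +1.5 | yes |
| +6 | +2.5 | yes |

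This does not depend on looking at one anterior point only. A woman with Aa +3 and Ba +6 who gains 3.5 cm at each ends at Aa -0.5 and Ba +2.5. She passes at both anterior points and still meets the extent criterion for entry.

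**2. Threshold out of reach (needs the assumption on L).** Largest gain = start - L. The threshold cannot be met when start - L ≤ 3, that is, start ≤ L + 3.

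| Limit L | Largest gain from -1 | Largest gain from 0 | Eligible starts that cannot pass |
|---|---|---|---|
| -3 | 2 | 3 (not more than 3) | -1 to 0 |
| -3.5 | 2.5 | 3.5 | -1 to -0.5 |
| -4 | 3 (not more than 3) | 4 | -1 only |
| -5 | 4 | 5 | none |

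At L = -3, a start of +1 allows a gain of 4 cm, so the threshold can be met from there.

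**3. C and D.** Three statements stand side by side. The success rule scores C and D. The exclusion list removes apical prolapse. The eligibility definition, Background and Discussion treat the middle compartment as part of the target. If apical descent is out, a supported apex has little room to rise more than 3 cm; if middle-compartment descent is in, scoring C and D is natural. The article supports both readings, and it gives no baseline C or D values to put figures on either.

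**The case against.** The strongest reply is that the text never says all four points must improve. A reader might infer from the word joining the points that it does, and go on to conclude that POP success would be close to zero in both arms and that the endpoint could not separate them. The documents do not support that chain. The combination rule is unstated, no baseline values or success rates are given, and women whose anterior points start below the hymen can succeed or fail and so remain informative. Failures fixed at baseline fall on both randomised arms; they cost power and clarity rather than favour one arm.

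It can also be said that scoring C and D fits a trial that targets the middle compartment, so removing them would prejudge an open question. That is right. What stands is the conflict in the eligibility text.

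Third, the -3 cm limit is not in the article. That is also true, and part 2 is conditional on it. Part 1 is not.

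Finally, the combination rule and the visit may be set in a fuller document. That would settle the ambiguity but not the defect, because the threshold is stated here as a change with no end position. Under any combination rule, part 1 holds for each anterior point starting beyond +2, and part 2 means that Aa and Ba cannot contribute a pass for women starting at 0 or higher up.

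**Conclusion.** The concern holds for the change-only definition of POP success. From the article's own figures, any point starting beyond +2 cm can meet the threshold and still lie in the trial's prolapse range, which contradicts the label of cure. Assuming the POP-Q limit of -3 cm, women whose anterior points start from -1 to 0 cannot meet the threshold at those points; the affected span narrows as the limit moves up and vanishes at -5 cm. The passages on apical and middle-compartment prolapse and on C and D must be reconciled.

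The proportion of women misclassified cannot be computed, because no baseline distribution is given. Whether a woman who passes at Aa and Ba counts as an overall success depends on the unstated combination rule. The stated primary hypothesis and the sample size concern continence, so the SUI comparison is unaffected. POP repair nevertheless has primary status, and its rule should be corrected.

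**What to change.** - Define POP success by final position at one prespecified follow-up visit, using the trial's own entry limit: Aa and Ba both more than 1 cm above the hymen, that is, below stage II as the article defines it. Under this rule Ba at +2.5 after surgery is a failure, and every eligible start can reach success if the limit is -3 cm.
- Report change in Ba, adjusted for baseline Ba, as a supportive analysis.
- Reconcile the eligibility definition with the exclusion of apical prolapse. Then state whether C and D count towards success and, if so, by what final position. This has to come before the rule is final: if the middle compartment alone can qualify a woman, Aa and Ba could already be past the limit at entry.

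The cost is a documented amendment to a primary endpoint definition after recruitment has begun (22 August 2016, Study design), made before unblinding. No new measurements are needed, because Table 1 already schedules the prolapse examination at baseline and at every follow-up visit.
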